## 9. Statistical Analyses

### 9.1. Power Analysis

The sample size was estimated with respect to the measurement of the main outcomes of the study, and the measure that required the largest sample size (HAM-D) was taken as the reference. Specifically, a sample size sufficient to reduce the total HAM-D score by 10%, with a two-tailed probability of 0.05% and a power of 90%, was estimated. The multicenter design of the study required an adjustment of the sample size estimate in accordance with the value of the intracluster correlation coefficient, set at 0.030, and the coefficient of variation of cluster sizes, set at 0.400. The estimated sample size is 176 patients, 88 for each arm. Based on previous studies conducted with similar patient populations, a dropout rate of 15% is expected. Therefore, it will be necessary to recruit 384 families, 192 for each arm. Each participating center is expected to recruit 16 families (8 for each arm).

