### 9.2. Statistical Analyses

The statistical analyses will be conducted in accordance with the intention-to-treat analysis. Missing data will be handled using a last observation carried forward (LOCF) analysis. Descriptive statistics will be calculated for the dependent and confounding variables for both groups. Confidence intervals will be calculated at 95%.

The analytical plan will include the following: (1) the use of generalized estimating equations (GEEs), which will provide an estimation of the impact of the intervention on the primary and secondary outcomes while controlling for multiple confounders (i.e., age, gender, illness duration, number of previous relapses, severity of symptoms at baseline, previous psychiatric admissions, physical and mental comorbidities, presence of psychotic symptoms during acute phases, suicidality, pharmacological treatments); (2) the application of a structural equation model to identify possible mediators and moderators of intervention efficacy (i.e., specific temperamental profiles, the presence of childhood trauma and/or abuse, severity of symptoms at baseline, the patient’s psychosocial functioning at baseline, number of family members, the relatives’ coping strategies and levels of expressed emotions at baseline); and (3) the use of a multivariate logistic regression model to identify predictors of a poor response to the experimental intervention.

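### The target of 384 families does not follow from 176 patients and 15% dropout, and the significance level is printed as 0.05%

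*Protocol article*

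**What the plan says.** Section 9.1 (Power Analysis) sets out the sizing in one paragraph, in this order.

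- The HAM-D is the reference outcome because it needed the largest sample. The effect is described as "a sample size sufficient to reduce the total HAM-D score by 10" per cent.
- Error rates: "with a two-tailed probability of 0.05% and a power of 90%, was estimated".
- Adjustment for the multicentre design: "the intracluster correlation coefficient, set at 0.030", and "the coefficient of variation of cluster sizes, set at 0.400".
- Result: "The estimated sample size is 176 patients, 88 for each arm".
- Dropout and recruitment: "a dropout rate of 15% is expected. Therefore, it will be necessary to recruit 384 families, 192 for each arm".
- Each centre is then expected to contribute 16 families, 8 per arm.

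Section 3 (Methods) gives 24 centres and 1:1 allocation. The Abstract and the Discussion repeat 384, and the Discussion presents the large sample as a strength. Section 9.2 (Statistical Analyses) says: "Confidence intervals will be calculated at 95" per cent.

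**The concern.** The paragraph claims a derivation: 176 patients, 15% dropout, therefore 384. A 15% allowance raises a sample by a factor of about 1.18, whereas the printed step more than doubles it. No other reason for the step is given.

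The recruitment target, the power and the significance level are the figures by which readers judge the size of a trial, and here they do not form one consistent set. If 208 is enough for 90% power, the trial plans 176 more families than its own calculation asks for, without a stated reason. If 384 is the real requirement, then 176 or the dropout rate is wrong. The difference would matter if recruitment fell short, because nobody could say from the text whether 208, about 317 or 384 is the number that secures 90% power.

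The printed significance level is a separate fault. Read literally, 0.05% is 0.0005, which does not belong with 95% confidence intervals.

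**Working it through.** **Inputs.** From section 9.1: 176 patients (88 per arm), dropout 15%, target 384 (192 per arm), ICC 0.030, cluster-size CV 0.400, 16 families per centre, power 90%, two-tailed level printed as 0.05%. From section 3: 24 centres. From section 9.2: 95% confidence intervals. The article prints no design-effect formula. I assume the usual one for unequal clusters, DE = 1 + ((1 + CV²)m − 1) × ICC, with m the mean number per centre.

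**Can the 176 be reproduced?** No. The 10% effect is not tied to a HAM-D mean or SD, so 176 is taken as given.

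**Step 1: the printed chain (176 already cluster-adjusted).**
- 176/0.85 = 207.1, so 208 in total; 88/0.85 = 103.5, so 104 per arm.
- The cruder 176 × 1.15 = 202.4 gives 203.
- To get from 176 to 384 by dropout alone, the rate would have to be 1 − 176/384 = 54.2%.
- 384 − 208 = 176 families in excess, and 384/208 = 1.85.

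**Step 2: 176 read as not yet cluster-adjusted.**

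| m per centre | DE | 176 × DE/0.85 |
|---|---|---|
| 8 | 1.248 | 258.5 |
| 16 (as stated) | 1.527 | 316.1, so 317 (318 with equal arms) |
| 24 | 1.805 | 374 |

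None gives 384. That would need m ≈ 25.4. With m = 16 it would need 30% dropout (268.7/0.70 = 383.9), which the article does not state.

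**Step 3: alpha taken literally as 0.0005.** Rescaling 176 from 0.05 to 0.0005 multiplies it by 2.158: 380 before dropout and 447 after. This does not produce 384 with a 15% allowance either.

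**Step 4: the number that does match.** 24 centres × 16 families = 384 exactly.

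**Step 5: what 384 would deliver at alpha 0.05.** Evaluable patients: 384 × 0.85 = 326.4, or 13.6 per centre. Suppose 176 gives 90% power for the 10% effect, with the SD unchanged. Let r be the square root of (effective planned size / effective achieved size), each size divided by its design effect. Then 90% power is available for an effect of 10% × r, and power for the 10% effect is Φ(3.2415/r − 1.960), where 3.2415 = 1.960 + 1.2816.

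| How clustering was handled | r | Power for 10% | Effect at 90% power |
|---|---|---|---|
| 176 adjusted, DE the same at both sizes: √(176/326.4) | 0.734 | 99.3% | 7.3% |
| 176 adjusted at 7.33 per centre (DE 1.225), DE 1.443 at 13.6: √[(176/1.225)/(326.4/1.443)] | 0.797 | 98.2% | 8.0% |
| As above, but DE 1.527 at 16 | 0.820 | 97.7% | 8.2% |
| 176 unadjusted, DE 1.443: √(176 × 1.443/326.4) | 0.882 | 95.7% | 8.8% |
| 176 unadjusted, DE 1.527: √(176 × 1.527/326.4) | 0.907 | 94.7% | 9.1% |

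The range is therefore about 95–99% power for the 10% effect, or 90% power for an effect of about 7.3–9.1%.

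**The case against.** The strongest reply is that the error does no harm. The target exceeds anything that follows from the stated inputs, it agrees with 24 centres of 16 families, and the Abstract and Discussion repeat it consistently. This stands as far as direction goes. A reader might infer from a broken power paragraph that the trial is underpowered, but nothing printed supports that. A shortfall could arise only if 176 or the effect assumption were itself wrong, which the article does not allow one to check. The reply does not rescue the derivation, because the text offers 384 as the consequence of 176 and 15% dropout, not as a capacity figure.

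A second reply is that 0.05% is plainly a typing slip, given 90% power and 95% intervals. I agree. A reader might go further and compute that 88 per arm has only about 41% power at 0.0005, or that about 380 evaluable patients would be needed. Those figures size the effect at 0.05 and test it at 0.0005, a combination the article never states. Had 0.0005 been used throughout, 176 would have 90% power by construction. The slip is a wording error and does not explain 384.

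A third reply is that an article may leave the HAM-D mean, the SD and the intermediate steps to the full protocol. That is fair, and their absence is not part of this point. Condensation can explain missing steps, but not printed figures that contradict one another.

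**Conclusion.** The point holds as an error in the printed figures. With 176 as the cluster-adjusted requirement, which is how the paragraph's order reads, the dropout-inflated total is 208, not 384. With 176 as the unadjusted figure, it is about 317–318. Neither supports 384 as the size needed for 90% power. The match with 24 × 16 suggests that centre capacity set the number, but the article does not say so, and this remains an inference.

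The consequence is an unexplained excess of 176 families over 208, or of about 67 over 317. Statements that 384 gives 99.3% power or detects a 7.3% effect should not be taken as established: they hold only if 176 already contains the cluster adjustment and the design effect does not grow with centre size. The supportable statement is the range above. It rests on 176 being right for the 10% effect, on 15% loss, on alpha of 5%, and on the assumed design-effect formula.

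The 0.05% significance level conflicts with section 9.2 and is wrong as printed.

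**What to change.** In section 9.1:

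1. Print the two-tailed significance level as 5% (0.05).
2. Say whether 176 is before or after the adjustment for ICC and cluster-size variation.
3. Then choose one of two courses. Either state the dropout-inflated requirement: 208 (104 per arm) if 176 is adjusted, or about 317–318 if it is not. Or keep 384, give its real basis (such as 24 centres × 16 families), and restate the power it delivers, computed from the sponsor's own inputs. The 95–99% range given here is a guide to what to expect, not text to print.

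The cost is a few sentences in section 9.1. No extra patients are needed. The Abstract and Discussion need changing only if 384 itself changes.

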### 9.2. Statistical Analyses

The statistical analyses will be conducted in accordance with the intention-to-treat analysis. Missing data will be handled using a last observation carried forward (LOCF) analysis. Descriptive statistics will be calculated for the dependent and confounding variables for both groups. Confidence intervals will be calculated at 95%.

The analytical plan will include the following: (1) the use of generalized estimating equations (GEEs), which will provide an estimation of the impact of the intervention on the primary and secondary outcomes while controlling for multiple confounders (i.e., age, gender, illness duration, number of previous relapses, severity of symptoms at baseline, previous psychiatric admissions, physical and mental comorbidities, presence of psychotic symptoms during acute phases, suicidality, pharmacological treatments); (2) the application of a structural equation model to identify possible mediators and moderators of intervention efficacy (i.e., specific temperamental profiles, the presence of childhood trauma and/or abuse, severity of symptoms at baseline, the patient’s psychosocial functioning at baseline, number of family members, the relatives’ coping strategies and levels of expressed emotions at baseline); and (3) the use of a multivariate logistic regression model to identify predictors of a poor response to the experimental intervention.

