## 1. Introduction

Major depressive disorder (MDD) is the most common mental disorder, with prevalence rates ranging from 7.2% to 10.8% in the general population [1]. It is a highly recurrent disorder [2], with approximately 50% of patients experiencing a relapse after a first episode, 70% after a second episode, and 90% after a third one [3].

According to the World Health Organization, MDD is among the top 10 causes of disability worldwide, and it is associated with high personal and societal costs and a significant reduction in the quality of life of both patients and their relatives [4,5].

Caring for a patient with MDD can be highly demanding and cause significant distress in family members, as is evidenced by the high rates of divorce and the frequent financial difficulties found among patients with MDD and their family members [6]. Balkaran et al. report that the levels of subjective and objective burden experienced by relatives of patients with depression are significantly higher than those reported by the families of patients with other mental disorders, including schizophrenia and bipolar disorder [7]. Relatives of patients with MDD often report financial difficulties, reduced social activity, concerns about stigma and prejudice toward people with depression and their families, and feelings of loneliness [8,9,10,11,12].

Between 40 and 70% of relatives of patients with major depression develop clinically significant anxiety and/or depressive symptoms [13,14], though these tend to recede as the severity of the depressive symptoms in their ill relatives reduce [14]. Additionally, family members often report a lack of adequate information on how to interact with their loved one [15], along with high levels of expressed emotions, in particular emotional overinvolvement and criticism [16].

The few available data about the impact of dysfunctional family environments and the long-term outcomes of MDD indicate that high levels of family burden, expressed emotions, and dysfunctional coping strategies by family members have a significant impact on the long-term outcomes of patients with major depression [17]. Heru et al. [13] and Keitner et al. [18] found that patients with MDD living in families with high levels of expressed emotion and burden achieve a full functional recovery after an acute episode less frequently than those living in less problematic families.

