## 7. Assessment Time and Instruments

The following activities are planned for the first three months of the study: (1) the obtaining of approval from local ethics committees; (2) the training of mental health professionals in the interventions and in the use of evaluation tools; and (3) the implementation of the interventions. The recruitment of the patients and their relatives will take place between month 4 and month 12. The patients will be randomly assigned by the coordinating center only after the receipt of written informed consent. The implementation of the intervention will take place between month 3 and month 18. Assessments will be performed between month 3 and month 36. The timeline of the study is shown in Table 1.

The socio-demographic and clinical characteristics of the patients and their relatives will be collected at baseline through validated assessment instruments (Table 2). Researchers participating in the study will be blinded to patient allocation. All patients will be assessed at the following time points: baseline (T0); 6 months post-randomization (T1); 12 months post-randomization (T2); and 24 months post-randomization (T3). All data will be collected during paper and pencil interviews. Each assessment is expected to take about 90/120 min per patient and 60/90 min per relative. During the evaluation, if the participant feel distressed or exhausted, the assessment can be stopped and another appointment can be scheduled for the following 2/3 days.

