## 8. Anticipated Results

### 8.1. Primary Outcomes

We expect that, at the end of the intervention, the MDD patients in the experimental group will show a significant reduction in the severity of their depressive symptoms compared with those in the control group. Moreover, we also expect the treated patients to report an improvement in their functioning and an increase in their social network at six months (i.e., improvements in the number of weekly social contacts, practical and emotional support from their social network, and an improvement in the quality of their intimate supportive relationships). We expect that these results will be maintained after 12 and 24 months, albeit with a reduction in magnitude.

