### 8.2. Secondary Outcomes

We expect that, compared with those in the control group, the patients receiving the PFI will report a significantly lower number of relapses and hospitalizations after 12 and 24 months as well as improvements in their adherence to pharmacological treatments, quality of life (evaluated using the Manchester Short Assessment of Quality of Life), and coping strategies, and a reduction in their internalized stigma. With respect to coping strategies, we expect an increase in the relatives’ problem-oriented coping strategies (i.e., maintenance of social interests, involving the patient in social activities, positive communication with the patient, seeking information, talking with friends and/or relatives about the patient’s situation) and a reduction in emotion-focused coping strategies (i.e., collusion, avoidance, resignation, coercion, use of alcohol and/or drugs). Moreover, we expect reductions in objective and subjective family burden and improvements in expressed emotions and quality of life, both at the end of the intervention and at follow-ups.

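### Carrying the last observation forward for up to 24 months biases the arm comparison, in a direction that depends on when and in which arm patients leave

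*Protocol article*

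**What the plan says.** Section 9.2 fixes the method in one sentence: "Missing data will be handled using a last observation carried forward (LOCF) analysis". It pairs this with an analysis principle, "The statistical analyses will be conducted in accordance with the intention-to-treat analysis", and a model, "the use of generalized estimating equations (GEEs), which will provide an estimation of the impact of the intervention on the primary and secondary outcomes". No outcome or visit is treated differently.

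Section 7 places the assessments at baseline (T0) and at 6, 12 and 24 months after randomisation (T1, T2, T3). A baseline value can therefore stand in for a score 24 months later.

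Two other sections describe change over that period. The Introduction says of major depression: "It is a highly recurrent disorder". Section 8.1, having predicted gains at six months, adds: "We expect that these results will be maintained after 12 and 24 months, albeit with a reduction in magnitude". Section 8.2 expects "a significantly lower number of relapses and hospitalizations after 12 and 24 months" in the experimental arm.

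Section 9.1 expects 15% dropout and does not divide it by arm or visit.

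**The concern.** LOCF is accurate only if a patient's outcome stays where it was when last seen. The protocol expects otherwise: scores improve by T1, the difference between arms then narrows, and relapses occur throughout.

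Three distortions follow, and they do not all point the same way.

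- A patient lost before T1 enters every later visit with the baseline score, which contains no treatment effect.
- A patient lost after T1 enters T3 with the T1 or T2 score. If the effect wanes, this makes it look longer-lasting than it is.
- For relapses and hospitalisations, the patient schedule in Table 2 records the number of episodes and previous hospitalisations at each visit. Such a count, carried forward, treats all unobserved time as event-free.

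The filled-in values are also analysed as if they had been observed, so the standard errors ignore the uncertainty of imputation.

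Unequal loss is plausible from the design. Section 4 gives about 18 sessions over 4 to 6 months in one arm and five sessions at 7- to 10-day intervals in the other. The results most exposed are those at 24 months, which the Discussion presents as a particular contribution of the trial.

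**Working it through.** The plan gives no figure for the effect of LOCF, so there is none to reproduce. The check asks what LOCF would report when the truth is known.

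**Inputs from the protocol.** 192 patients per arm and 15% dropout (section 9.1), that is 0.15 × 384 = 57.6, about 58 patients; visits at 0, 6, 12 and 24 months (section 7); an effect that shrinks after T1 (section 8.1).

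**Assumptions, not in the protocol.** HAM-D SD 6, within-patient correlation 0.5, baseline mean 20, the control course, the effect sizes, the relapse risks, and dropout by arm and visit. Loss is random within arm. Negative differences favour PFI.

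**1. Balanced 15% loss after T1, half in each interval.** With true effects d1, d2, d3 at T1, T2, T3:

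LOCF effect at T3 = 0.85 × d3 + 0.075 × d1 + 0.075 × d2

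- Effects -2/-1.5/-1: -(0.85 + 0.15 + 0.1125) = -1.11, against a true -1.00.
- Effects -2/-1/0: -(0 + 0.15 + 0.075) = -0.225, against a true 0.

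Simulation gave -1.11 to -1.13 for the first case (coverage of the 95% interval about 94%) and -0.23 for the second (coverage about 92%).

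**2. Loss before T1, true T3 effect -1.0.** With loss fraction a in an arm:

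LOCF arm mean at T3 = (1 - a) × true T3 mean + a × 20

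| Loss PFI / control | Control course | PFI mean | Control mean | LOCF effect |
|---|---|---|---|---|
| 20% / 10% | 20 to 15 | 0.8×14 + 0.2×20 = 15.2 | 0.9×15 + 0.1×20 = 15.5 | -0.30 |
| 20% / 10% | 20 to 18 | 0.8×17 + 0.2×20 = 17.6 | 0.9×18 + 0.1×20 = 18.2 | -0.60 |
| 20% / 10% | unchanged | 0.8×19 + 0.2×20 = 19.2 | 20.0 | -0.80 |
| 15% / 15% | 20 to 15 | 0.85×14 + 0.15×20 = 14.9 | 0.85×15 + 0.15×20 = 15.75 | -0.85 |
| 10% / 20% | 20 to 15 | 0.9×14 + 0.1×20 = 14.6 | 0.8×15 + 0.2×20 = 16.0 | -1.40 |

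Simulated coverage was about 75% in the first row, 88% in the second, and 94% in the third and fourth.

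**3. Persistence, as the ratio of the T3 to the T1 effect.** Take balanced 15% loss and true effects of 1, 0.75 and 0.5 in units of the T1 effect. If all loss is before T1, LOCF gives 0.425 / 0.85 = 0.50, which is correct, although both effects are diluted. If all loss is between T1 and T2, it gives 0.85 × 0.5 + 0.15 × 1 = 0.575.

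**4. Relapse.** Assume 24-month risks of 30% (PFI) and 45% (control), constant hazard, and dropouts last seen at six months. Six-month risks are 1 - 0.70^0.25 = 8.5% and 1 - 0.55^0.25 = 13.9%. The true difference is -15.0 points.

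- 15% / 15% loss: 26.8% against 40.3%, difference -13.6.
- 20% / 10% loss (PFI / control): 25.7% against 41.9%, difference -16.2.
- 10% / 20% loss: 27.9% against 38.8%, difference -10.9.
- No true difference (45% in both arms), 20% / 10% loss: 38.8% against 41.9%, a spurious benefit of 3.1 points.

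The HAM-D simulations used 192 per arm and ANCOVA at T3 adjusted for baseline, standing in for the GEE. The hand calculations are differences in means and do not depend on that choice.

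**The case against.** The strongest defence is that the harm is small under the protocol's own expectations. With balanced 15% loss and an effect that fades but is maintained, the error is about 0.1 HAM-D point and coverage is about 94%. The 75% coverage needs a 20%/10% split, all of it before T1, and a five-point fall in controls. The protocol states none of these. A fall that large is also not obvious, because section 3 excludes patients with recent clinically relevant worsening. All of this stands.

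A reader might infer that LOCF necessarily overstates how long the effect lasts, or favours PFI on every outcome. The documents do not support that. They give no dropout by arm or visit. Loss before T1 dilutes the effect, balanced loss understates a relapse benefit, and unequal loss can push either way.

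A reader might also infer that patients whose intervention is stopped leave the trial. Section 4 ends the intervention on relapse or hospitalisation but does not say that assessments then end. The rule makes outcome-related loss plausible, not certain.

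The unseen analysis plan may contain sensitivity analyses, so their absence from the article is not the point. The point is the method that the article does fix. Nor does intention-to-treat require LOCF: multiple imputation keeps every randomised patient without freezing scores.

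**Conclusion.** The concern holds as a poorly chosen method whose bias has no predictable direction. LOCF conflicts with the protocol's own description of a recurrent illness and a waning effect, and it treats imputed values as data.

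The planned effect is a 10% HAM-D reduction, or 2 points on the assumed baseline of 20. Against that, the errors are about 0.11 points (6%) for balanced loss after T1 with a fading effect and 0.23 points (11%) if the effect vanishes. With unequal loss before T1 they reach 0.70 points (35%) of understatement or 0.40 points (20%) of overstatement. The first two are modest; the last two need a 20%/10% imbalance, in one direction or the other, and a five-point fall in controls.

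These sizes rest on assumed HAM-D values and dropout patterns, and on loss that is random within arm. Loss related to outcome could be worse, and would affect other methods too.

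**What to change.** Replace LOCF as the primary method in section 9.2 with one of the following:

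- a mixed model for repeated measures on all observed T1 to T3 scores, with arm-by-visit and baseline-by-visit terms; or
- GEE on multiply imputed data, or weighted GEE, under missing at random. Unweighted GEE on observed data alone would in general need data missing completely at random, so deleting LOCF is not enough.

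Analyse relapses and hospitalisations as time to first event, or as counts with observed follow-up time as an offset.

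Add a sensitivity analysis for outcome-related dropout, because section 4 ties stopping the intervention to relapse or hospitalisation. Keep LOCF at most as a further sensitivity analysis.

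The cost is a change of wording, slightly more programming, and slightly wider standard errors. Design and data collection do not change. The change should be made before unblinding.

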Patients with intellectual disabilities will not be eligible, and neither will patients who experience a clinically relevant worsening of psychiatric symptoms (i.e., requiring a substantial change in the therapeutic dosage of psychiatric medications or access to emergency care or hospitalization) during the two months before recruitment. Patients with comorbid physical illnesses will not be excluded from the study unless the physical condition is so severe and disabling as to require intensive medical care. All recruited patients will continue to receive the treatments usually provided in their centers, which include regular outpatient psychiatric assessments, pharmacological treatments, and management of the side effects of medications. All patients will receive an adequate pharmacological treatment according to the NICE [51] guidelines for the whole duration of the study.

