## 4. Interventions

The experimental intervention will consist of the Falloon psychoeducational family intervention, which was developed for the treatment of schizophrenia [52], but which we have adapted for the treatment of major depression. The experimental intervention will be administered individually to each recruited family and consist of the following six phases: (1) engagement of the family unit; (2) individual assessment; (3) family assessment; (4) informative sessions; (5) communication skills sessions; and (6) problem-solving skills sessions.

The informative sessions will deal with the following issues: (1) clinical characteristics of MDD, symptoms, prognosis, risk and protective factors; (2) available pharmacological and non-pharmacological treatments for MDD, indications, side effects and strategies to cope with them, treatment duration, risk factors for relapse, and effects related to abrupt cessation of the therapy; and (3) early warning signs. A specific informative session on suicide risk has been developed, and this will be administered only to patients who report suicidal ideation during the intervention or who have a history of suicide attempts or ideation.

The sessions will take place three times a month for a period ranging from 4 to 6 months (about 18 sessions in total). The number of sessions, as well as their frequency, may vary depending on each patient’s clinical situation. Sessions will have an average duration of 60–90 min and will require the active participation of all family members, including the patient. Between sessions, participants will be invited to organize “family meetings” to discuss the topics covered during the previous meeting, progress made, and problems encountered in implementing changes. Each meeting will ideally be divided into three phases: a first phase dedicated to clarifications and questions regarding the topics previously discussed, a second phase focused on the main topic of the meeting (the so-called “teaching phase”), and a final phase in which the key points addressed during the session are summarized and in which “homework” is assigned.

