The control group will receive an educational five-session intervention, administered every 7–10 days, on the following topics: healthy lifestyle (diet and nutrition), stress management, regulation of circadian rhythms, and the management of medication side effects. The control group sessions will last 60–90 min and will be as interactive as possible. At the end of each session, participants will receive leaflets and cards summarizing the key-points addressed during the session.

Treatment fidelity among the different centers will be secured by the development of manuals for both interventions and by continuous supervision, either on site or via phone calls.

The interventions will be discontinued under the following circumstances: (1) if patients or their relatives are unable to attend more than five consecutive psychoeducational sessions; (2) if patients are hospitalized or experience any affective relapse during the intervention; or (3) if patients or relatives withdraw their consent.

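### LOCF with no HAM-D between baseline and month 6 analyses patients who miss T1 at their baseline score, which can shrink or distort the primary comparison

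*Protocol article*

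**What the plan says.** Section 9.2 plans an intention-to-treat analysis by GEE and gives one missing-data rule: "Missing data will be handled using a last observation carried forward (LOCF) analysis". It does not limit the rule by outcome, visit or reason.

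Section 7 fixes the visits: "All patients will be assessed at the following time points: baseline (T0); 6 months post-randomization (T1"), then T2 at 12 months and T3 at 24 months. The HAM-D row of Table 2 lists those four points and no others.

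Section 8.1 expects that "at the end of the intervention, the MDD patients in the experimental group will show a significant reduction in the severity" of depressive symptoms compared with control. The intervention lasts 4 to 6 months, so T1 is the visit that tests this.

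Three further passages matter:
- Section 3 excludes patients with "clinically relevant worsening of psychiatric symptoms" "during the two months before recruitment".
- Section 4 discontinues the intervention "if patients are hospitalized or experience any affective relapse during the intervention". It does not say that assessments stop.
- The intervention periods differ. PFI sessions run "three times a month for a period ranging from 4 to 6 months". For the comparator, "The control group will receive an educational five-session intervention", with 7 to 10 days between sessions.

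**The concern.** LOCF is least defensible when the carried value is the pre-treatment one, and before T1 this schedule offers nothing else. A patient who improved and then missed T1 loses the improvement. A patient who relapsed and then missed T1 is entered at a score taken before the relapse, and recent worsening is an exclusion, so that score comes from a relatively stable period. Someone who leaves before T1 and never returns carries baseline to T2 and T3 as well.

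At stake is the HAM-D comparison on which the trial was sized. Hidden improvement pulls a true benefit towards zero. Hidden relapse flatters whichever arm has more relapsers missing T1. A reader of the results could not tell which had happened.

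**Working it through.** **1. What the plan's figures give.** The plan states no figure for the effect of LOCF and no HAM-D mean or SD. Section 9.1 gives 384 patients and 15% dropout: 0.15 × 384 = 57.6, so about 58 patients, or about 29 per arm. The 15% has no time point and follow-up runs to month 24, so this is an upper bound on missing T1.

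**2. Hidden improvement.** Let a share m miss T1 in both arms regardless of outcome, and let them benefit like the others. LOCF enters change 0 for them, so estimated difference = (1 − m) × true difference. With m = 0.15 the factor is 0.85. Section 9.1 targets a 10% reduction; at an assumed mean of 15 to 20 this is 1.5 to 2.0 points. Then 0.85 × 1.5 = 1.28 and 0.85 × 2.0 = 1.70.

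**3. Unequal missingness.** Let mE and mC be the shares missing T1 (PFI, control) and rE and rC their true mean changes. Bias in the difference (PFI minus control; negative favours PFI) = −(mE·rE − mC·rC). It is zero only when the two products are equal. Illustration, all values assumed, with patients who attend changing by −6 (PFI) and −4 (control) and the same r in both arms:

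| Missing PFI / control | True change in those missing | True difference | LOCF | Bias |
|---|---|---|---|---|
| 15% / 15% | +3 to +8 | −1.70 | −1.70 | 0 |
| 20% / 10% | +3 to +8 | −0.90 to −0.40 | −1.20 | −0.3 to −0.8 |
| 10% / 20% | +3 to +8 | −2.50 to −3.00 | −2.20 | +0.3 to +0.8 |
| 20% / 10% | −4 | −1.60 | −1.20 | +0.4 |

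**4. One possible relapse route.** Suppose relapsers whose intervention was stopped miss T1 with probability m1 and other relapsers with probability m0. Six months is 182.6 days. PFI runs 4 to 6 months (mid share 0.833). Control has 4 gaps of 7 to 10 days, 28 to 40 days (mid share 34/182.6 = 0.186). Error towards PFI = relapse rate × rise × (0.833 − 0.186) × (m1 − m0). With an assumed 20% relapse and an 8-point rise still present at T1, the coefficient is 0.2 × 8 × 0.647 = 1.04:

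- m1/m0 = 0.5/0: 0.52 towards PFI
- 0.5/0.25: 0.26 towards PFI
- 0.5/0.4: 0.10 towards PFI
- 0.5/0.5: zero
- 0.25/0.5: 0.26 against PFI

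Over 10 to 30% relapse and 6 to 10 points, the coefficient runs from 0.1 × 6 × (0.667 − 0.219) = 0.27 to 0.3 × 10 × (1 − 0.153) = 2.54.

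**5. Would simpler alternatives help?** Same mid case, no true effect, non-relapsers changing by −3 with 5% of them missing T1, m1/m0 = 0.5/0.

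- *Available cases only.* PFI: attending non-relapsers 0.8 × 0.95 = 0.76, attending relapsers 0.2 × (1 − 0.833 × 0.5) = 0.117; mean = (0.76 × −3 + 0.117 × 8)/0.877 = −1.54. Control: attending relapsers 0.2 × (1 − 0.186 × 0.5) = 0.181; mean = (−2.28 + 1.451)/0.941 = −0.88. Error −0.66, no better than LOCF at −0.52.
- *Imputation with relapse status known for everyone.* Error about zero, if relapsers who miss T1 resemble those who attend.
- *Imputation where, among those missing T1, only relapses during the intervention are recorded.* An unrecorded relapser is imputed at −3 instead of +8, an 11-point error. Arm error = 11 × 0.2 × 0.647 × m0 = 1.42 × m0 against PFI: 0.36 at m0 = 0.25 and 0.71 at m0 = 0.5. With m1 = 0.5, LOCF errs by 0.26 and 0 there, so this version is worse than LOCF.

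**The case against.** A reader might infer that a known relapse is always analysed as no change. The document does not support that. The rule in section 4 stops the intervention, section 7 schedules all patients for T1 to T3, and section 9.2 plans intention to treat. A relapser who attends T1 is analysed at the observed score.

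A reader might also infer that LOCF favours PFI, because relapse can stop PFI over a much longer period. That needs stopped relapsers to miss T1 more often than other relapsers, and nothing in the document says so. Relapse rate, rise, m1 and m0 are all assumed, and the error is zero when m1 equals m0. This objection stands in full.

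On dilution, the 15% is not tied to T1, and shrinkage is conservative. Holding the variance unchanged, an effect at 85% needs 176/0.85² = 244 patients. If a design effect of 1.527 (16 per centre, ICC 0.030, CV 0.400) still had to be applied, it needs 372. Both are below 384, so power is not clearly lost, although 176 cannot be checked without an SD. The estimate is still biased towards zero.

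The calculations compare arms at T1, whereas GEE can use all visits, and someone who misses T1 but attends T2 or T3 contributes real scores there. That softens the point for an effect pooled over visits; it does not change what is entered at T1.

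Finally, Table 2 records episodes and hospitalisations at the same visits that are missed and lists no relapse date. Imputing on relapse status therefore cannot be assumed to work without extra care. This stands and shapes the fix.

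**Conclusion.** The point holds in a limited form. That a missed T1 HAM-D is replaced by baseline follows directly from sections 7 and 9.2 and Table 2, with no assumption. It is a method that the article chooses, not a detail left to a later analysis plan.

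The consequence for a true effect is shrinkage to as little as 85%, assuming that up to 15% miss T1 in both arms regardless of outcome and would have benefited like the rest. The consequence for relapse is confined to patients who both relapse and miss T1. Any additional arm bias has unknown size and direction; in the assumed mid case it runs from 0.52 points towards PFI to 0.26 against, and it vanishes if missingness among relapsers balances.

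The rule should be changed, because a better one is available at little cost. Confidence is medium, since the practical size depends on how many patients miss T1 and why.

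**What to change.** In section 9.2, replace LOCF as the primary rule with multiple imputation by arm, feeding the planned GEE. The imputation model should contain baseline HAM-D, the covariates of the GEE, available later HAM-D scores, and relapse or hospitalisation status by month 6.

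Use relapse status only where it is obtained the same way in both arms: from the treating physician, relatives or centre records, or asked retrospectively at T2. Table 2 already lets the researcher turn to other sources, such as the physician or relatives, when the patient's information is inadequate. Do not take it from the record of stopped interventions, which covers 4 to 6 months under PFI but only about 4 to 6 weeks in control.

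Keep LOCF as a sensitivity analysis, and add one that varies the imputed scores of those missing T1 over a stated range. GEE on available cases alone is not an adequate replacement.

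The cost is a little more analysis work and a check of existing clinical records for patients who miss T1. Visits and sample size do not change.
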